### Concealment mechanism {16b}

The IMP kit codes will be captured onto RedCap ensuring that the trial team and participants remain blind to treatment allocation.

### Implementation {16c}

Randomisation will be done through the RedCap database using stratification in which patients will first be grouped into strata according to the following factors: age, gender, obesity, symptomatic or asymptomatic, smoking, and vaccination status. Within each stratum, patients will be randomly assigned to one of the two arms of the study.

Following the pre-screening telephone contact before screening/baseline visit, the clinical investigator or delegate will enter the participant’s initials, and all the factors stated above. and confirm participant eligibility on the RedCap secure online system and allocate the appropriate PIN to the patient.

Delegated staff at participating sites will be provided with a secure login to the RedCap website, according to their role in the trial. The randomisation result will be shown directly online as a unique IMP kit code, with an email confirmation sent to the user and to the trial team. The investigator will provide details of the allocated unique kit code assigned to the participant on the prescription. Delegated staff will collect the allocated IMP kit from pharmacy on behalf of the participant ahead of the screening/baseline visit.

Randomisation will be considered complete after the participant has signed the consent form and ingests their first dose of trial medication during screening/baseline visit. Participants who withdraw before taking their first dose will be considered withdrawn prior to randomization.

## Assignment of interventions: blinding

### Who will be blinded {17a}

Participants and investigators will both be blinded to treatment allocation (double-blinded). All IMP will be packaged and labelled to maintain blinding, and blinded IMP kit codes will be used to identify the medication. IMP kit codes will be linked to the PIN allocated to the participant at randomisation.

### Procedure for unblinding if needed {17b}

A member of the CINVESTAV team will unblind the participant’s trial treatment allocation when:Emergency unblinding is deemed necessary for appropriate clinical management.The participant reports overdosing on study medication and is hospitalised as a result.When a SUSAR needs to be submitted to the regulatory agencies within pre-specified timelines.

## Data collection and management

### Plans for assessment and collection of outcomes {18a}

Each participant will be given a unique trial Participant Identification Number (PIN). Data will be collected at the time points indicated in the Participants Timeline (See item {13}).

### Plans to promote participant retention and complete follow-up {18b}

Participants will be in regular contact by phone and text message during the trial duration. They will receive a telephone call on day 5 to schedule their next visit, provide instructions for dose intake on day 7, and verify the nose swab and temperature daily collection as well as the intake of IMP and log registries. The research member will inquire about any clinical events that may require further clinical assessment.

Participants will have two follow-up visits on day 7 and day 14 and will be assessed by the trial team, undergo blood tests for toxicity and pharmacokinetic assessment (on day 7 only), and provide stool samples. These visits can be done in clinic if the participants have completed their isolation period.

Participants will have a telephone follow-up 3 weeks after their last day of treatment (day 7). The research team will enquire about any relevant clinical events that may require further clinical assessment and collect further information through a questionnaire.

### Data management {19}

Data will be entered onto paper Case Report Forms (CRFs) or directly onto the RedCap database. Staff will receive training on data collection. Paper CRFs will be placed in clear plastic wallets which allow reading both sides of the CRF without opening the wallets. The plastic wallets will be decontaminated before leaving the participant's residence as per infection control guidance.

Identification logs, screening and enrolment logs will be kept at the trial site in a locked cabinet within a secured room.

Research team members across all participating sites will receive training on the FANTAZE protocol and on the data entry in the approved FANTAZE database.

All data will be handled in accordance with the Federal Law on Protection of Personal Data Held by Individuals 2010, the Data Protection Act 2018 and the GDPR 2016/679 including all further updates.

### Confidentiality {27}

Adequate measures will be in place to ensure all participant data collected are secure. CRFs will record the participant initials and month/year of birth but not their name. The only link between the PIN and the participant’s name will be on the screening log kept at site and accessed only by the site trial team.

Data will be recorded on the CRFs and entered onto the FANTAZE custom-designed database under this identification number. The database will be password protected and only accessible to members of the FANTAZE trial team at UCL, trained and authorised site staff, and external regulators if requested. The servers are protected by firewalls and are patched and maintained according to best practice.

The physical location of the servers is protected by security door access.

Blood samples will be labelled with the FANTAZE participant identification number ensuring the pseudonymity of the participants who have provided the samples. At the laboratories, brief clinical details will be stored including age and sex. Blood results will be stored on a web-based, secure confidential database, including after completion of the FANTAZE trial.

### Plans for collection, laboratory evaluation and storage of biological specimens for genetic or molecular analysis in this trial/future use {33}

#### Pharmacokinetic sampling

Sample timing: Samples will be drawn for pharmacokinetics on day 7 (Table 3). Participants will be telephoned on Day 5 by the trial site team to receive instructions and arrange the day 7 visit time. The participant will take the medication as instructed by the trial member. The participant will take the dose before the visit and record the time to the nearest minute. The next dose should be taken during the study visit. Before taking the next dose of IMP, a blood sample will be drawn, and time to the nearest minute will be recorded. Once the predose sample has been taken, the participant will take the next dose and record the time to the nearest minute. Two more blood samples will be drawn 30 and 60 minutes after taking the medication. Time to the nearest minute will be recorded on each sample. All samples will be identified with the participant´s PIN, date, and time to the nearest minute. Processing of samplesSafety bloods (full blood count, urea and electrolytes, liver function tests and uric acid)—sent to the Medical Research Unit in Immunology and Infectology at the National Medical Centre Hospital of Infectology “La Raza” for standard assays.Serum for storage—sent to the Medical Research Unit in Immunology and Infectology at the National Medical Centre Hospital of Infectology “La Raza” and processed by the laboratory staff: sample centrifuged and supernatant stored at −70 °C.Diagnostic nasopharyngeal swab—sent to the Medical Research Unit in Immunology and Infectology at the National Medical Centre Hospital of Infectology “La Raza” for standard PCR assay for SARS-CoV-2.Nose swab and stool samples for viral load measurement and viral sequencing will be sent to the Medical Research Unit in Immunology and Infectology at the National Medical Centre Hospital of Infectology “La Raza” for extraction and storage. Nose swab samples will be kept in a transport medium and stored at 5°C for up to three weeks prior to analysis. Stool samples will be extracted and kept at −70°C prior to analysis.Nose swab and stool sample viral load measurements will be done at Hakken Enterprise Laboratories.Nose swab and stool samples viral sequencing will be done at UCL.

**Table 3 Tab3:** Laboratory samples to be collected during the trial

Sample	Day 1	Days 2–6	Day 7	Day 14
Blood samples	• Full blood count (3mL) • Urea and electrolytes, liver function tests, uric acid (7mL) • Serum for storage (10mL) Plasma base line pharmacokinetic samples (1X2 mL)		• Full blood count (3mL) • Urea and electrolytes, liver function tests, uric acid (7mL) • Serum for storage (10mL) • Plasma Pharmacokinetic samples (3×2mL)	• Full blood count (3mL) • Urea and electrolytes, liver function tests, uric acid (7mL) • Serum for storage (10mL)
Nasopharyngeal swab (*only if COVID-19 testing not done yet)*	• Diagnostic sample			
Nose swab	Sample for viral load measurement/viral sequencing	Sample for viral load measurement/viral sequencing taken daily [self- sampled]	Sample for viral load measurement/viral sequencing	
Stool samples			Sample for viral load measurement/viral sequencing	Sample for viral load measurement/viral sequencing

## Statistical methods

### Statistical methods for primary and secondary outcomes {20a}

Summary of baseline characteristics, by trial arms, will be by frequency and percentage for categorical variables, and for continuous variables by mean and standard deviation (or median and inter-quartile range for non-normally distributed data).

The primary endpoint will be analysed using a linear mixed-effect model, including the main effects (each experimental treatment) as factors, and the interaction between them. Baseline values of viral load will be included for each subject and, linked within subjects using random intercept terms.

An analysis of covariance (ANCOVA) will also be performed: the ANCOVA model will use the viral load on Day 5 as the dependent variable and include the baseline value as independent variable.

Secondary endpoints include binary endpoints and continuous endpoints (note that the pharmacokinetic analysis of favipiravir and nitazoxanide is described in a separate section below).

For binary endpoints, a logistic regression will be used. The adjustment strategy will be the same as the primary endpoint.

The comparison of duration of fever following commencement of medication between trial arms will be by t-test, or non-parametric equivalent depending on the distribution of the data. Regression models will also be used to perform analyses adjusted for site (as random effect.).

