**Methods:**

Trial design: Phase IIA randomised, double-blind, 2 × 2 design, placebo-controlled, interventional trial.

Randomisation: Participants will be randomised 1:1 by stratification, with the following factors: gender, obesity, symptomatic or asymptomatic, current smoking status presence or absence of comorbidity, and if the participant has or has not been vaccinated. Blinding: Participants and investigators will both be blinded to treatment allocation (double-blind).

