**Discussion:**

We propose to conduct a proof-of-principle placebo-controlled clinical trial of favipiravir plus or minus nitazoxanide in health workers, their household members and patients treated at the Mexican Social Security Institute (IMSS) facilities. Participants with or without symptomatic COVID-19 or who tested positive will be assigned to receive favipiravir plus nitazoxanide or favipiravir plus nitazoxanide placebo. The primary outcome will be the difference in the amount of virus (‘viral load’) in the upper respiratory tract after 5 days of therapy. Secondary outcomes will include hospitalization, major morbidity and mortality, pharmacokinetics, and impact of antiviral therapy on viral genetic mutation rate. If favipiravir with nitazoxanide demonstrates important antiviral effects without significant toxicity, there will be a strong case for a larger trial in people at high risk of hospitalization or intensive care admission, for example older patients and/or those with comorbidities and with early disease.

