## Introduction

### Background and rationale {6a}

In viral infections such as influenza, it is well recognized that early antiviral therapy is associated with improved clinical outcomes. Using drugs with differing modes of action is a fundamental principle of antimicrobial chemotherapy and is used across the spectrum of infectious diseases (for example in HIV, tuberculosis, multi-drug resistant bacteria and invasive fungal disease).

The antiviral drug favipiravir is active against a broad range of viruses and has shown promising results in COVID-19 disease in two small Chinese studies [1, 2]. The drug works similarly to remdesivir (another promising treatment for COVID-19), but unlike remdesivir (which is intravenous) it has a well-established and currently available oral formulation with a good safety profile. Furthermore, both Royal Free Hospital and Great Ormond Street Hospital (London) involved in this trial are amongst the only UK groups with direct clinical experience of this drug, having successfully used favipiravir to treat other viral infections.

The results of the early studies [1, 2] on favipiravir in COVID-19 urgently need to be confirmed or refuted in a high-quality placebo-controlled trial.

Another antiviral with potential activity in COVID-19 is nitazoxanide. Nitazoxanide and its active metabolite, tizoxanide, are active against a variety of bacteria and have also been found to have activity against many DNA and RNA viruses. Nitazoxanide acts as an antiviral at the step after favipiravir in that it inhibits blocks maturation of the viral nucleocapsid N protein and therefore viral assembly [3]. It has also been suggested that nitazoxanide may have non-specific beneficial effects including innate immune system boosting and damping late immune and inflammatory responses [3, 4].

Favipiravir and nitazoxanide have different mechanisms of action so given together are likely to act at least additively, and possibly synergistically, providing a strong rationale for a trial which examines combination therapy.

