### Trial design {8}

FANTAZE is a phase IIA randomised, double-blind, placebo-controlled, interventional trial.

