### Sample size {14}

We have conducted extensive power calculation and power simulation exercises for the proposed design [6]. In the proposed design 120 participants (108 evaluable participants, which implies a 10% allowance for attrition and other methodological challenges) will be recruited, so that half of the participants receive both favipiravir/nitazoxanide treatment, and the other half receive favipiravir/nitazoxanide placebo treatment. We hypothesised that around a 1 log10 difference in viral load by day 5 would be clinically significant.

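### The primary model has two treatment main effects and their interaction, but both arms receive favipiravir, so only the effect of adding nitazoxanide can be estimated

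*Protocol article*

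**What the plan says.** Section {20a} of the protocol article says that the primary endpoint will be analysed with a "linear mixed-effect model, including the main effects (each experimental treatment) as factors, and the interaction between them". Baseline viral load is included, with random intercepts for subjects. An ANCOVA of day 5 viral load on the baseline value is planned in addition. Binary secondary endpoints get logistic regression, with an adjustment strategy described as the same as for the primary endpoint.

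The Methods paragraph of the abstract describes the trial as a "Phase IIA randomised, double-blind, 2 × 2 design, placebo-controlled, interventional trial", and the keywords also carry the 2 × 2 label. The Trial design section {8} leaves it out: "FANTAZE is a phase IIA randomised, double-blind, placebo-controlled, interventional trial".

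The arms are described consistently in other sections:
- The Discussion paragraph of the abstract has participants "assigned to receive favipiravir plus nitazoxanide or favipiravir plus nitazoxanide placebo".
- The Sample size section {14} has "half of the participants receive both favipiravir/nitazoxanide treatment, and the other half receive favipiravir/nitazoxanide placebo treatment".
- The Implementation section {16c} has each patient "randomly assigned to one of the two arms of the study".
- The Objectives section {7} names one comparison, the combination against favipiravir alone.
- The Intervention description {11a}, including Table 1, gives active favipiravir in both arms and mentions a placebo for nitazoxanide only.
- The Recruitment section {15} gives 60 participants per arm.

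**The concern.** A model with two treatment main effects and an interaction belongs to a four-cell trial in which each drug is given and withheld. Here no one is randomised to go without favipiravir. Two of the stated terms therefore have no data behind them, and the sentence that defines the primary analysis does not match the trial.

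Two things are at stake. First, the published specification of the primary model is unusable as it stands. Software will either stop on a one-level factor or drop aliased columns by its own rule. Second, the column that is kept decides the name of the result: the same number could be printed as a nitazoxanide main effect or as a favipiravir-by-nitazoxanide interaction. That label matters here because the Background section {6a} raises possible synergy, which this design cannot test.

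**Working it through.** **Inputs.** Arms: favipiravir + nitazoxanide, and favipiravir + nitazoxanide placebo ({7}, {11a}, {14}, {16c}). Recruited: 120, 60 per arm ({15}). Evaluable: 108, with a 10% attrition allowance ({14}), so 108 / 2 = 54 per arm. Model terms: intercept, favipiravir (F), nitazoxanide (N) and F×N ({20a}).

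**The plan's own figure.** 108 / (1 − 0.10) = 120, as stated. The article gives no SD, alpha or power behind the 108. Nothing below depends on them.

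**Design matrix.** With 1 for active and 0 for not active, there are only two distinct rows:

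| Arm | Intercept | F | N | F×N |
|---|---|---|---|---|
| Favipiravir + nitazoxanide | 1 | 1 | 1 | 1 |
| Favipiravir + placebo | 1 | 1 | 0 | 0 |

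The F column equals the intercept column, and the F×N column equals the N column. Over 54 + 54 participants the rank is 2 for 4 columns. More participants only repeat the same two rows, so the rank does not change with sample size.

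**What can be estimated.** Write the coefficients as b0, b1 (F), b2 (N) and b3 (F×N).
- Mean in the combination arm: b0 + b1 + b2 + b3.
- Mean in the favipiravir + placebo arm: b0 + b1.
- Difference between arms: b2 + b3.

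A linear combination is estimable only if its vector lies in the row space, which is spanned by (1,1,0,0) and (0,0,1,1). Checking each:

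| Quantity | Two stated arms | Four-cell 2 × 2, for reference |
|---|---|---|
| b1, favipiravir | no | yes |
| b2, nitazoxanide | no | yes |
| b3, interaction | no | yes |
| b0 + b1 | yes | yes |
| b2 + b3 | yes | yes |

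The intercept b0 alone, vector (1,0,0,0), is outside the row space as well. Under this coding none of the four coefficients is individually estimable. The one estimable treatment quantity is b2 + b3, the effect of nitazoxanide given favipiravir.

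**Does another form of the model rescue it?**
- Effect coding gives rows (1,1,1,1) and (1,1,−1,−1): rank 2 of 4.
- Adding time (baseline, day 5) and all its interactions with treatment gives rank 4 of 8, so repeated measures do not help.
- A baseline covariate or a random intercept does not separate treatment columns that are identical.
- A true four-cell 2 × 2 has rank 4 of 4, which confirms that the stated terms fit that design and not this one.

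**After the change.** With intercept and N only, the treatment part has rank 2 of 2. The N coefficient is then the difference between the arms.

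**The case against.** The strongest reply is that little is lost in practice. The contrast in the Objectives section survives, with the same estimate, standard error and p-value whichever aliased columns are removed. Software that enters main effects before interactions will usually keep the nitazoxanide term. A failure on a one-level factor would be seen and corrected. The planned ANCOVA can answer the question with one arm term. Randomisation, sample size and data collection are untouched.

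Most of this stands, and it limits the point. It does not remove it. The article states a primary model that contradicts its arms, so a statistical analysis plan would have to override that model rather than fill in detail. The ANCOVA is an additional analysis, and the terms named for it are the outcome and the baseline; no treatment factor is written there either.

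A reader might infer more than the documents support, in four ways:
- **That the primary question cannot be answered.** It can, through b2 + b3.
- **That the logistic models contain the same error.** The article says only that the adjustment strategy is shared, which may mean covariates and not treatment terms. Fever duration is compared between trial arms, which suits two arms.
- **That the trial claims to confirm or refute favipiravir.** The Background section says that early favipiravir results "urgently need to be confirmed or refuted in a high-quality placebo-controlled trial". That is a statement of need. The comparator section {6b} and the main Discussion come closer, because they draw the rationale for this trial from a similar sentence, but neither makes it an objective.
- **That the abstract promises a test of the combination against no treatment.** It says "If favipiravir with nitazoxanide demonstrates important antiviral effects without significant toxicity, there will be a strong case for a larger trial", but this follows a description of the two arms and an outcome defined as a difference in viral load. It can fairly be read as effect relative to the favipiravir arm.

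**Conclusion.** The point holds for the primary-model sentence and for the 2 × 2 label. The treatment part of the stated model has rank 2 of 4, so a favipiravir effect and an interaction cannot be estimated at any sample size. This rests only on the two arms as the article describes them and needs no assumption about SD, alpha or power.

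The consequence is bounded: the effect of adding nitazoxanide to favipiravir remains estimable and is the comparison in the primary objective. Mislabelling it as an interaction is a possibility, not a certainty. The wrongly stated primary model must be corrected. The wording on favipiravir's own efficacy and on the case for a larger trial needs a minor clarification at most.

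**What to change.** 1. In {20a}, replace the two main effects and their interaction with one treatment factor: nitazoxanide versus nitazoxanide placebo, both on favipiravir. If the model is longitudinal, include treatment-by-time and say that the day 5 contrast is the primary estimate.
2. Name the same single factor in the ANCOVA and in the logistic models, so that nothing has to be inferred from the shared adjustment strategy.
3. Delete the 2 × 2 label from the abstract and the keywords.
4. As a minor clarification, word the conclusions and the case for a larger trial as the effect of adding nitazoxanide to favipiravir. State in the rationale (Background {6a}, comparator section {6b} and main Discussion) that no randomised comparison in this trial tests favipiravir itself.

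The cost is wording. The sample size stays at 120 recruited and 108 evaluable, and no procedure or data collection changes. The claims become narrower, in line with the stated primary objective.

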### Outcomes {12}

The primary outcome is the upper respiratory tract viral load at day 5.

Method of measurement: quantitative polymerase chain reaction (PCR) performed on nose swab samples.

The secondary outcomes are the following:Percentage of participants with undetectable upper respiratory tract viral load after 5 days of therapy.

Method of measurement: quantitative polymerase chain reaction (PCR) performed on nose swab samples.Proportion of participants with undetectable stool viral load after 7 days of therapy and 14 days post-randomisation.

Method of measurement: PCR performed on stool samples.Rate of decrease in upper respiratory tract viral load during 7 days of therapy.

Method of measurement: PCR performed on daily nose swab samples.Duration of fever following commencement of medication.

Methods of measurement: daily body temperature records between Day 1 and Day 7 post- randomization.Proportion of participants with hepatotoxicity after 7 days of therapy and 14 days post-randomisation.

Method of measurement: standard diagnostic laboratory assays for liver transaminases, alkaline phosphatase and bilirubin.Proportion of participants with other medication-related toxicity after 7 days of therapy and 14 days post-randomisation.

Methods of measurement: determination of medication-related adverse events by investigators.Proportion of participants admitted to hospital with COVID-19-related illness.

Methods of measurement: participant self-report, review of hospital records and discharge summaries.Proportion of participants admitted to ICU with COVID-19-related illness.

Methods of measurement: participant self-report, review of hospital records and discharge summaries.Proportion of participants who have died with COVID-19-related illness.

Methods of measurement: next of kin report, review of hospital records and discharge summaries.Pharmacokinetic and pharmacodynamic analysis of favipiravir and tizoxanide.

Method of measurement: assay of favipiravir and tizoxanide levels in plasma at day 7 of therapy. All participants from each arm will provide a pre-dose trough sample and a post-dose (30 to 60 min) sample on Day 7 of therapy. A nonlinear mixed effects model will be fitted jointly to favipiravir and tizoxanide pharmacokinetic and viral load (pharmacodynamic) data.

The model will estimate the following primary PK parameters:

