### Recruitment {15}

The trial will be advertised at each site and the participant identification centre and health workers provided with the trial team’s contact details. Occupational Health teams at each participating centre will be provided with the trial information which they can provide to health workers who consult them. Potential participants will also be approached after research on databases. 120 participants will be recruited in total (60 participants in each arm) over an overall period of 6 months.

Should recruitment targets be slower than anticipated other clinics, hospitals, and diagnostic laboratories in México City and its suburban area will be approached to enroll participants, which will be done centrally by the trial team in any case.

Recruitment will be monitored regularly to identify any barriers to recruitment. Reporting will be conducted on a regular basis over the trial set-up and recruitment period to the Trial Management Group (TMG), and trial oversight committees. Remedial action will be put in place as soon as any concerns have been raised.

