### Methods in analysis to handle protocol non-adherence and any statistical methods to handle missing data {20c}

The primary analysis will be on the intention-to-treat (ITT) population. There will be no imputation for missing data for any of the study outcomes.

A modified ITT analysis will be performed that will only include participants who have a confirmed diagnosis at baseline of SARS-CoV-2 infection (diagnostic swab and nose swab samples collected at Baseline).

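### Two analyses of day 5 viral load are prescribed without saying which decides, and the one listed first cannot be fitted as written in a two-arm trial

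*Protocol article*

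**What the plan says.** Outcomes {12} fixes one endpoint at one time: "The primary outcome is the upper respiratory tract viral load at day 5".

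Statistical methods {20a} gives two analyses of it. The first: "The primary endpoint will be analysed using a linear mixed-effect model, including the main effects (each experimental treatment) as factors, and the interaction between them". On baseline it adds: "Baseline values of viral load will be included for each subject and, linked within subjects using random intercept terms". The second: "An analysis of covariance (ANCOVA) will also be performed: the ANCOVA model will use the viral load on Day 5 as the dependent variable", with the baseline value as the independent variable. Neither is called primary, supportive or sensitivity.

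The section on non-adherence and missing data {20c} does rank the populations: "The primary analysis will be on the intention-to-treat (ITT) population", with a modified ITT analysis beside it. It names no model and rules out imputation.

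On arms, Intervention description {11a} and Sample size {14} give active favipiravir to everyone; only nitazoxanide versus its placebo is randomised. Recruitment {15} states: "120 participants will be recruited in total (60 participants in each arm) over an overall period of 6 months".

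**The concern.** Two different models of one endpoint will usually give different estimates and p-values. If one is significant and the other is not, the article does not say which counts, and the choice could be made after the data are seen.

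The natural way out is to take the first-listed model as the lead, but that model does not fit this trial. Its factorial terms presuppose arms with and without favipiravir, and no arm is without it. It also states no day term, although it links baseline and later values through a random intercept. Following the text as written therefore gives a lead analysis that is partly inestimable, or diluted once the inestimable terms are dropped, beside an ANCOVA that addresses the stated endpoint directly.

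The Discussion paragraph of the Abstract says important antiviral effects without significant toxicity would make the case for a larger trial, so the reading of this one comparison matters.

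**Working it through.** **Inputs from the article.** "120 participants (108 evaluable participants, which implies a 10% allowance for attrition and other methodological challenges) will be recruited". Check: 108 / 0.90 = 120, which reproduces the recruited number; 108 / 2 = 54 evaluable per arm. Sample size {14} takes a difference of about 1 log10 by day 5 as clinically significant.

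**Assumed, because not stated.** Two-sided α = 0.05; SD 2 log10 at baseline and at day 5; baseline-to-day-5 correlation ρ = 0.3, 0.5, 0.7.

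**Step 1: estimability.** Let F and N indicate active favipiravir and active nitazoxanide. Both arms have F = 1, so the F column equals the intercept and F×N equals N. The model with F, N and F×N has four coefficients but only two distinct arm means. Only the nitazoxanide contrast can be estimated.

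**Step 2: the surviving tests.** Let b and d be the arm differences in mean viral load at baseline and day 5, and k = 2 × √(2/54) = 0.385.

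- ANCOVA: d − ρb, with SE = k√(1−ρ²) and expected value 1.
- Mixed model, literal reading (one arm effect over baseline and day 5): (b+d)/2, with SE = k√((1+ρ)/2). Its expected value is 0.5, because the baseline difference is zero under randomisation.
- Mixed model, change-from-baseline reading (arm-by-day term): d − b, with SE = k√(2(1−ρ)) and expected value 1.

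The correlation with the ANCOVA test is √((1−ρ)/2) for the literal reading and √((1+ρ)/2) for the change reading.

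**Step 3: example, ρ = 0.5.** The SEs are 0.333 (ANCOVA), 0.333 (literal) and 0.385 (change). The expected z values are 1/0.333 = 3.00, 0.5/0.333 = 1.50 and 1/0.385 = 2.60. Power is 0.85, 0.32 and 0.74.

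**Step 4: bivariate normal results.** 'Either' is the chance under no effect that at least one test is significant. 'Disagree' is the chance, at a true 1 log10 effect, that exactly one is.

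| ρ | Reading | Test correlation | Power, mixed model / ANCOVA | Disagree | Either |
|---|---|---|---|---|---|
| 0.3 | literal | 0.59 | 0.36 / 0.78 | 45% | 0.088 |
| 0.5 | literal | 0.50 | 0.32 / 0.85 | 55% | 0.091 |
| 0.7 | literal | 0.39 | 0.29 / 0.95 | 67% | 0.094 |
| 0.3 | change | 0.81 | 0.59 / 0.78 | 23% | 0.078 |
| 0.5 | change | 0.87 | 0.74 / 0.85 | 15% | 0.073 |
| 0.7 | change | 0.92 | 0.92 / 0.95 | 5% | 0.068 |

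**Step 5: a favourable reading.** If the mixed model takes baseline and day 5 as outcomes but holds the two baseline means equal, its day 5 contrast is essentially d − ρb, the ANCOVA contrast. In simulation (54 per arm, SD 2, 20,000 runs per setting) the test correlation under no effect was about 0.997–0.998, the either-one error about 0.05, and disagreement at 1 log10 about 1–2%.

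**The case against.** **The wording already implies an order.** The text says "The primary endpoint will be analysed using a linear mixed-effect model" and introduces the ANCOVA with 'also'. The same section handles fever duration in the same way: a t-test first, then regression models as an addition. This stands as an inference about intent. It does not settle the matter, because the model it would put in the lead cannot be fitted as written.

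**Labels belong in the statistical analysis plan.** This is a condensed article, and a missing label alone would be no finding. The point rests on what the article states: two analyses of one endpoint, the first with terms that the two-arm design cannot support.

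**The false-positive rate.** A reader might infer that the plan nearly doubles the error rate. The article does not support that. It states no alpha and proposes no claim on whichever test succeeds. Figures near 0.09 come from particular readings of an underspecified model; the change reading gives 0.07–0.08, and the equal-baseline reading almost no inflation.

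**Opposite conclusions.** A reader might also infer effects in opposite directions. What was calculated is one test significant and the other not.

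**The large disagreement comes from a poorly built mixed model.** This is correct: the 45–67% reflects its dilution. That is why the two points are taken together here, and why the 5–23% is shown beside it.

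**A phase IIA proof-of-principle trial has no significance-based go rule.** Also correct, which limits the consequence. The reported primary result would still depend on an unsettled choice.

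**Conclusion.** The point holds in a limited form. The article prescribes two analyses of day 5 viral load, does not say which decides, and lists first a model whose favipiravir main effect and interaction are inestimable. That conclusion needs no assumptions.

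The size does depend on assumptions the article does not state (two-sided 5%, SD 2 log10, ρ 0.3–0.7), with 54 evaluable per arm. At a true 1 log10 effect, disagreement on significance runs from about 1–2% on the equal-baseline reading, through 5–23% on the change reading, to 45–67% on the literal one. At ρ = 0.5 the literal mixed model has power 0.32 against 0.85 for the ANCOVA. An either-one claim would carry an error of about 0.07–0.09 on the literal and change readings, but the plan makes no such claim. The change is worth making before unblinding.

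**What to change.** In Statistical methods {20a}, name one deciding analysis: the ANCOVA of day 5 log10 viral load on arm (nitazoxanide versus nitazoxanide placebo, both with favipiravir) and baseline viral load, in the ITT population. It is already planned and takes the stated primary outcome as its dependent variable.

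Keep the mixed model as a sensitivity analysis that cannot carry the efficacy conclusion alone. Remove the favipiravir main effect and the interaction, and add a treatment-by-day term from which the day 5 contrast is read.

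The cost is a few sentences before unblinding, with no extra participants or data. There are two downsides. The ANCOVA drops anyone without a baseline or day 5 value, since {20c} allows no imputation, whereas a mixed model on the daily swabs could retain some of them. And a significant mixed model could no longer support the conclusion if the ANCOVA were not significant.
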